### Recruitment {15}

EGN is detected by upper gastrointestinal endoscopy performed at either the referral or participating institutions involved in this study. Patients are required to visit the outpatient clinic for an explanation of ESD prior to treatment. The investigators then review the eligibility and exclusion criteria for all potential patients. The recruitment period has been designed for two years. The number of eligible patients at all institutions per month is estimated to be approximately 20. Assuming a 30% consent rate, enrollment is expected to be completed in 2 years.

## Assignment of intervention: allocation

### Sequence generation {16a}

Upon obtaining patient consent, the investigator will register the patient in the database of the UMIN Medical Research Support Cloud version, UMIN INDICE Cloud, which serves as a web-based central randomization system. Each patient will be assigned a unique identification number for registration. The registration process will only be accepted if all the required data are provided. After confirming the eligibility on the registration screen, a registration number will be generated. The UMIN INDICE cloud will facilitate both immediate and concealed allocations. Registered patients will be randomized (1:1) into either the SCM-ESD or FCM-ESD groups using dynamic balancing, employing a minimization method based on tumor location (upper or middle third of the stomach vs. lower third of the stomach), tumor size (0–20 mm vs. > 20 mm), and the use of thrombotic agents (presence vs. absence).

### Concealment mechanism {16b}

A web-based central randomization system with a validated password will ensure concealment of the randomization sequence.

### Implementation {16c}

A web-based central randomization system will generate randomization using an allocation sequence. One investigator will oversee the randomization system, but will not participate in patient enrollment or study treatment.

## Assignment of interventions: blinding

### Who will blinded {17a}

Neither the patients nor investigators will be blinded to the allocated treatment.

### Procedure for unblinding if needed {17b}

Not applicable, as this study is unblinded.

## Data collection and management

### Plans for assessment and collection of outcomes {18a}

The investigator will gather data, including general information, eligibility criteria, and exclusion, at the time of registration. Perioperative and postoperative data will be inputted by the investigator, referencing medical records as appropriate. All registration and outcome information will be stored in the UMIN INDICE Cloud.

### Plans to promote participant retention and complete follow-up {18b}

Upon registration, all assessments of study outcomes and follow-up will be conducted during the hospital stay. Furthermore, follow-up on procedure-related adverse events will be continued for six months after treatment. The principal investigator will continuously monitor the retention rate.

### Data management {19}

Each investigator will register and input data into the UMIN INDICE cloud. The investigators must ensure that the data are accurate and complete. The principal investigator will confirm data adequacy. The data are stored in the UMIN INDICE cloud and accessible only to research personnel trained in confidentiality and privacy.

### Confidentiality {27}

All data stored in the UMIN INDICE cloud will be protected from access by third parties by setting identification numbers and passwords, encryption using 128 bits SSL and VPN, double firewalls, and a monitoring system for unauthorized access and intrusion. No information that can easily identify the individuals is stored in the dataset. The correspondence sheet linking the patient and identification number will be stored in a lockable box. All information retrieved from the cloud will be stored on a computer with a password set for 10 years after the completion of the trial.

### Plans for collection, laboratory evaluation, and storage of biological specimens for genetic or molecular analysis in this trial/future use {33}

Investigators will obtain informed consent from the patients to collect biological samples for histopathological assessment. These samples will be securely stored in a freezer within a locked laboratory for at least five years following the completion of the study and then properly disposed of in accordance with each institution’s Standard Operating Procedures for the Storage of Samples and Information Obtained from Human Subjects. Any secondary use of the samples and information in future trials will be conducted only after obtaining written consent from the participants and receiving approval from the Institutional Review Committee for the new trial protocol.

## Statistical methods

### Statistical methods for primary and secondary outcomes {20a}

With regard to the primary outcome as the completion of ESD with the knife alone, the two groups will be compared using the Cochran-Mantel–Haenszel test stratified by lesion location (upper or middle third of the stomach vs. lower third of the stomach), lesion size (0–20 mm vs. 21 mm or more), and presence of antithrombotic agents (continued, discontinued, or not administered). If SCM-ESD significantly outperforms FCM-ESD (two-sided significance level of 5%), we will conclude that SCM-ESD is a more useful treatment method than FCM-ESD.

With regard to secondary outcomes, the number and duration of hemostasis using hemostatic forceps and procedure time will be analyzed using the Wilcoxon rank-sum test. The speed of dissection, thickness of the submucosal layer in the resected specimen, and volume of the submucosal injection solution will be analyzed using *t*-tests. En bloc resection, complete resection, curative resection, severe thermal damage to the resected specimen, type of submucosal injection solution, operator change, and occurrence of adverse events will be analyzed using Fisher’s exact test.

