### Objectives {7}

This study aims to investigate the hemostatic efficacy of SCM-ESD and FCM-ESD in patients with EGN.

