As for ESD procedure, in principle, ESD will be performed for en bloc resection of a target lesion using an electrosurgical knife. However, if en bloc resection is not feasible owing to certain circumstances, alternative strategies such as piecemeal resection or additional ablation techniques such as argon plasma coagulation or hot biopsy may be employed to prevent residual tissue. After identifying the lesion, circumferential marking dots will be made placed approximately 2–3 mm outside the lesion using the tip of the knife. An injection needle will then be introduced from outside the markings, and a viscous solution will be injected into the submucosal layer beneath the lesion. After confirming elevation of the lesion, an initial mucosal incision will be made outside the marking using a knife. After completing the circumferential mucosal incision, submucosal dissection will be initiated using a knife. Traction assistance can be provided in the direction of the operator. Additional local injections can be administered using either the injection needle or the tip of the knife as the mucosal incision or submucosal dissection progresses. The volume of solution injected from the injection needle will be recorded. Dissection will continue until the lesion is excised with a knife. In cases of bleeding during mucosal incision or submucosal dissection, initial hemostasis will be attempted by coagulation with the tip of a knife. However, if bleeding cannot be controlled using a knife alone, hemostatic forceps will be employed as a rescue device. Forceps will be used to grasp the bleeding vessels, followed by coagulation. The criteria for transitioning to hemostatic forceps are as follows: (i) complete hemostasis cannot be achieved within 30 s using the knife; (ii) if the operator determines that bleeding is difficult to control with the knife alone; or (iii) if the operator determines that dealing with the exposed vessel using the knife alone is challenging. Transitioning to hemostatic forceps will be permitted if (ii) or (iii) is met, even if (i) is not fulfilled, to ensure patient safety. If hemostatic forceps are employed, hemostasis with the forceps will continue until the bleeding is completely stopped. The number and duration of hemostatic forceps used will be also recorded. The use of other devices that are not regulated may be allowed based on the operator’s judgment and such instances will be recorded.

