### Outcomes {12}

The primary outcome is successful completion of ESD using an electrosurgical knife alone, which is considered an important indicator reflecting the hemostatic ability to control intraoperative bleeding. If hemostatic forceps are required as a rescue device to achieve hemostasis prior to tumor retrieval, the procedure will be considered a failure. Secondary outcome includes the number and duration of hemostasis performed with hemostatic forceps; procedure time, including total ESD time, mucosal incision time, and submucosal dissection time; speed of submucosal dissection; en bloc resection rate; complete resection rate; curative resection, evaluated based on endoscopic curability (A or B); degree of each endoscopic curability category; thickness of the submucosal layer in the resected specimen; type and volume of submucosal injective solution used; occurrence of operator change; and adverse events. Total ESD time is divided into mucosal incision time and submucosal dissection time. The continuous outcome data will be analyzed without any categorization.

Outcome without histopathological assessments will be evaluated at ESD. Outcomes with histopathological assessments including complete resection rate; curative resection, evaluated based on endoscopic curability (A or B); degree of each endoscopic curability category; and thickness of the submucosal layer in the resected specimen will be evaluated within 1 week after ESD.

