## Discussion

This trial aims to provide evidence supporting the superiority of hemostatic ability in SCM-ESD compared with FCM-ESD for patients with intramucosal EGN. Completion of ESD with the knife alone, without the use of hemostatic forceps as the primary outcome measure, can be achieved when bleeding control using the knife is sufficient during ESD. The higher completion rate in SCM-ESD indicates that the bleeding control ability using the knife is superior to that of conventional FCM-ESD. The number and duration of hemostasis with hemostatic forceps, as secondary outcomes, also reflect the hemostatic ability of the knife during ESD. If bleeding control with the knife is better, the number and duration of hemostasis with hemostatic forceps can be expected to decrease, even when needed. Additionally, other secondary outcome measures, such as procedure time, en bloc and complete resection rates, and adverse events, will provide a comprehensive understanding of the potential advantages of SCM-ESD over FCM-ESD.

In conclusion, the findings of this multicenter randomized controlled trial are expected to provide valuable evidence on the hemostatic efficacy of SCM-ESD compared with FCM-ESD in patients with intramucosal EGN. These results could lead to the adoption of SCM-ESD as the preferred treatment method for EGN, potentially improving the safety and reliability of ESD procedures.

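### The decision rule turns a significant result on knife-only completion into a claim of overall usefulness, which is broader than the hemostatic ability that the endpoint measures

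*Protocol article*

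**What the plan says.** The Protocol article, Statistical methods for primary and secondary outcomes {20a}, compares the groups on the primary outcome with a stratified Cochran-Mantel-Haenszel test. It then states a rule with one condition, significance in favor of SCM-ESD at the two-sided 5% level, and one consequence: "we will conclude that SCM-ESD is a more useful treatment method than FCM-ESD".

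Other sections describe what the endpoint measures more narrowly:

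- Objectives {7}: "This study aims to investigate the hemostatic efficacy of SCM-ESD and FCM-ESD in patients with EGN".
- Outcomes {12}, on the primary outcome: "which is considered an important indicator reflecting the hemostatic ability to control intraoperative bleeding". The failure definition concerns use of a device: "If hemostatic forceps are required as a rescue device to achieve hemostasis prior to tumor retrieval, the procedure will be considered a failure".
- Discussion: "The higher completion rate in SCM-ESD indicates that the bleeding control ability using the knife is superior" to that of conventional FCM-ESD. The same paragraph gives procedure time, resection rates and adverse events the task of completing the picture of SCM-ESD's advantages.

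Those further outcomes are secondary. Section {20a} assigns Wilcoxon tests to procedure time and to the number and duration of forceps hemostasis, t-tests to three continuous measures, and Fisher's exact test to resection outcomes, specimen thermal damage and adverse events. None of them appears in the decision rule.

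**The concern.** A pre-specified conclusion should claim no more than its endpoint can show. Knife-only completion says whether bleeding was controlled without a rescue device. Usefulness as a treatment also depends on how long the procedure takes, whether the resection is curative, the state of the specimen and what harm is done. The rule goes from the first to the second without consulting the outcomes that carry the second.

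Followed as written, a trial in which SCM-ESD needed forceps less often but took longer, gave fewer curative resections or caused more adverse events would still meet the condition for declaring it the more useful method. The wording matters because the closing paragraph of the Discussion foresees SCM-ESD becoming the preferred method on the strength of these results.

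**Working it through.** **1. The sections side by side.**

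| Section | What a good primary result is said to show |
|---|---|
| Objectives {7} | hemostatic efficacy |
| Outcomes {12} | ability to control bleeding during the procedure |
| Discussion | better bleeding control with the knife |
| Statistical methods {20a} | greater usefulness as a treatment method |

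Three of the four agree. Only the decision rule goes further, and it is the sentence that fixes the trial's conclusion.

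**2. What the trial was sized for.** Inputs from Sample size {14}: pilot FCM-ESD rate 34.6% (9/26), assumed gain 25 points, two-sided alpha 5%, power 80%, chi-square test. The section does not state the control rate used. I take the pilot rate, so p1 = 0.346, p2 = 0.596 and mean p = 0.471.

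n per group = [1.96 × √(2 × 0.471 × 0.529) + 0.842 × √(0.346 × 0.654 + 0.596 × 0.404)]² / 0.25² = (1.384 + 0.575)² / 0.0625 ≈ 61.4, rounded up to 62.

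This matches the stated 62 per group, with power 80.4%. Taking 37.5% versus 62.5% also gives 62. The calculation is sound, and it concerns knife-only completion only.

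**3. What that size can say about harm (illustration).** The article gives no adverse event rates, so every rate here is an assumption. Exact power of Fisher's test at 62 per arm is the sum, over all pairs of event counts (i, j), of Bin(i; 62, pF) × Bin(j; 62, pS) for the pairs with Fisher p ≤ 0.05. Here pF and pS are the assumed FCM-ESD and SCM-ESD rates.

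| Assumed rates, FCM-ESD vs SCM-ESD | Power |
|---|---|
| 1% vs 2% | 0.1% |
| 2% vs 4% | 1.2% |
| 3% vs 6% | 3.6% |
| 5% vs 10% | 9.3% |
| 10% vs 20% | 25.9% |
| 5% vs 15% | 34.3% |

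With 65 per arm the doubling rows run from 0.1% to 27.6%. At a true 5% in both arms, the half-width of the 95% interval for the difference is about 1.96 × √(2 × 0.05 × 0.95 / 62) = 7.7 points. Zero events among 62 patients leaves an upper limit of 1 − 0.025^(1/62) = 5.8% (two-sided 95% Clopper-Pearson).

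So a non-significant harm comparison at this size would leave a doubling of adverse events quite possible, and could not by itself carry a claim of overall usefulness. The calculation covers adverse events only. It says nothing about procedure time, curative resection or thermal damage.

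**The case against.** The strongest reply is that context already narrows the sentence. It closes a paragraph about the primary outcome, the article frames its question as hemostatic efficacy throughout, and the Discussion gives the intended reading. The secondary outcomes are collected and compared between the groups, so a worse result would be visible. This shows that the authors probably mean the narrower claim. It does not change the rule, which names a broader one and gives the other outcomes no part in it.

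Several stronger readings are tempting and should not be drawn:

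- *That the plan will disregard worse secondary results.* The rule is silent on how they weigh. It does not say they will be set aside.
- *That the plan will take a non-significant harm test as proof of equal safety.* No section says so. Interim analyses {21b} invokes safety only to justify having no interim look, and rests on previous studies and the pilot.
- *That the trial is too small.* Low power for uncommon harms is usual in an efficacy trial of this size, and the stated sample size reproduces.
- *That leaving confidence intervals or a thermal-damage grading unstated is a fault.* Naming a test does not exclude estimates, and such details are commonly left to the full protocol or SAP, which are not shown.
- *That the thermal damage mismatch strengthens this point.* Section {20a} tests "severe thermal damage to the resected specimen", which the list in Outcomes {12} does not contain. The inconsistency is real, but it has no bearing on how broad the decision rule is.

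**Conclusion.** The point holds as one about the scope of the pre-specified conclusion. A significant result on knife-only completion supports superior hemostatic ability, as three other sections of the article say. It does not by itself support greater overall usefulness. This rests on comparing the sections and needs no assumed figure.

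No stated number is wrong. The harm calculation only illustrates why non-significant adverse event comparisons could not fill the gap. It depends on assumed rates, although the message is the same for every doubling from a control rate of 1% to 10% (power at most about 26% at 62 per arm). The matter is worth correcting because it alters what the trial may conclude. It touches no test, population or sample size.

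**What to change.** Reword the consequence in section {20a} along these lines: *if the primary test is significant in favor of SCM-ESD, the conclusion will be that SCM-ESD has superior hemostatic ability, shown by a higher rate of ESD completed with the knife alone.* Add that any statement about overall usefulness will be made only after considering the between-group estimates for procedure time, curative resection, severe thermal damage and adverse events, and that a non-significant harm comparison will not be offered as support for it.

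Separately, reconcile Outcomes {12} with section {20a} on severe thermal damage, so that the outcome list and the analysis agree.

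The change needs no new patients, and the outcomes concerned are already in the plan. Recruitment is complete (Trial status), so it can be made in the analysis and reporting documents. The price is a narrower headline claim.

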### Sample size {14}

In our previous pilot study comparing the outcomes of SCM-ESD and FCM-ESD for the same subjects as in this study, the completion rate of ESD with the electrosurgical knife alone in SCM-ESD was 62.5% (40/64) compared to 34.6% (9/26) in FCM-ESD, resulting in a difference of 27.9%. Considering the variability in ESD outcomes among institutions, we assumed a 25% additive effect of SCM-ESD over FCM-ESD on the completion rate. The required number of cases was determined using the *χ*^2^ test with a two-sided alpha significance level of 5% and a power of 80%, resulting in a total required number of 62 case per group (124 cases in total). Considering a dropout rate of approximately 5% for ineligible patients, we calculated that 65 patients per group (130 patients in total) would be required.

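### Continuous and count secondary outcomes get unadjusted tests after minimised allocation, which costs power to the extent that the minimisation factors are prognostic

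*Protocol article*

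**What the plan says.** Under Sequence generation {16a}, patients are allocated 1:1 by dynamic balancing, "employing a minimization method based on tumor location" (upper or middle versus lower third), tumor size (up to 20 mm versus larger) and antithrombotic use (present versus absent).

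Under Statistical methods for primary and secondary outcomes {20a}, the primary outcome is compared with a Cochran-Mantel-Haenszel test stratified by the same three variables, with antithrombotic use in three categories instead of two. The next paragraph turns to the secondary outcomes: "the number and duration of hemostasis using hemostatic forceps and procedure time will be analyzed using the Wilcoxon rank-sum test". It continues: "The speed of dissection, thickness of the submucosal layer in the resected specimen, and volume of the submucosal injection solution will be analyzed using" t-tests. The binary outcomes get Fisher's exact test. None of these tests has strata or covariates.

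The additional-analyses section {20b} plans subgroup analyses by the same factors, among others. These split the comparison but do not adjust it. The section on non-adherence and missing data {20c} adds no adjusted analysis.

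**The concern.** Minimisation makes the arms nearly equal on the three factors, so the outcome variation due to those factors largely cancels from the difference between arms. A t-test or rank-sum test does not know this and leaves that variation in its standard error. If the factors predict the outcome, the standard error is too large, the true type I error falls below 5%, and real differences are missed more often than with an adjusted test.

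The affected outcomes matter to the trial's interpretation. The Discussion says that the number and duration of forceps hemostasis also reflect the knife's hemostatic ability, and it counts procedure time among the outcomes that will round out the picture. The plan treats the three factors as important in allocation, in the primary test and in subgroups, but not in the overall secondary comparisons.

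**Working it through.** **The plan's own figure.** The article gives a sample size for the primary outcome only. Inputs: "two-sided alpha significance level of 5% and a power of 80" percent; control rate 34.6% (9/26); "we assumed a 25% additive effect of SCM-ESD over FCM-ESD on the completion rate", so 34.6% versus 59.6%, mean 47.1%.

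n = [1.96·√(2·0.471·0.529) + 0.842·√(0.346·0.654 + 0.596·0.404)]² / 0.25² = (1.384 + 0.575)² / 0.0625 ≈ 61.4, so 62 per group. This matches "resulting in a total required number of 62 case per group (124 cases in total"). For dropout, 62 × 1.05 = 65.1 and 62 / 0.95 = 65.3; the stated 65 agrees within rounding. No power is stated for any secondary outcome, so the rest uses 62 per arm with assumed outcome models.

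**Size of an unadjusted test under balance.** Let R2 be the share of outcome variance explained by the three factors. With the factors balanced, the true standard error is √(1−R2) times the one the test uses, so

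size = 2·[1 − Φ(1.96/√(1−R2))].

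**Power, two conventions.**
- Residual SD fixed (assumed 0.5 on the log scale, effect 0.25). SE = 0.5·√(2/62) = 0.0898 and 0.25/0.0898 = 2.784. Adjusted power = Φ(2.784 − 1.96) = 79%. Unadjusted power = Φ(2.784 − 1.96/√(1−R2)).
- Total SD fixed, with the effect giving 80% power at R2 = 0. Unadjusted power = Φ(0.842/√(1−R2)). Adjusted power = Φ(2.802/√(1−R2) − 1.96).

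| R2 | Size, unadjusted | Power, residual SD fixed: unadjusted vs adjusted | Power, total SD fixed: unadjusted vs adjusted |
|---|---|---|---|
| 0 | 5.0% | 79 vs 79% | 80 vs 80% |
| 0.1 | 3.9% | 76 vs 79% | 81 vs 84% |
| 0.2 | 2.8% | 72 vs 79% | 83 vs 88% |
| 0.3 | 1.9% | 67 vs 79% | 84 vs 92% |
| 0.5 | 0.6% | 50 vs 79% | 88 vs 98% |

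**Simulation with minimisation carried out.** Settings: 124 patients, 80% biased coin, three two-level factors with assumed prevalences 0.5, 0.3 and 0.2, and 2,000 runs. Log procedure time has residual SD 0.5, arm effect 0.25 and a common coefficient b for each factor, so R2 = 0.62b²/(0.62b² + 0.25). The forceps count is overdispersed Poisson with factor and arm effects twice as large; it is not fitted to the pilot. R2 refers to log time.

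| b (time ratio per factor, e^b) | R2 | Time, size: Wilcoxon vs rank ANCOVA | Time, power | Count, power |
|---|---|---|---|---|
| 0 (1.0) | 0 | 4.8 vs 4.9% | 77 vs 78% | 34 vs 33% |
| 0.2 (1.22) | 0.09 | 4.1 vs 4.8% | 74 vs 78% | 39 vs 41% |
| 0.4 (1.49) | 0.28 | 1.9 vs 4.2% | 64 vs 77% | 41 vs 49% |
| 0.6 (1.82) | 0.47 | 1.0 vs 5.2% | 49 vs 75% | 34 vs 53% |

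A van Elteren test was simulated with the same residual SD and arm effect. At R2 of 0.17 / 0.31 / 0.44 its power was 73 / 75 / 74%, against 70 / 63 / 52% for Wilcoxon and 78 / 79 / 78% for regression. At R2 = 0 it lost about 3 to 4 points.

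**Binary outcomes.** For an uncommon event, Fisher's test ran at about 2% with or without prognostic factors. Its conservatism there comes mainly from discreteness.

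**The case against.** The strongest reply is that nothing decisive depends on this. The conclusion rests on the primary outcome, which is stratified. Only that outcome is powered, and the error in the secondary tests is in the safe direction. This stands, and it limits how serious the point is.

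Second, the documents give no R2. An R2 of 0.28 in the simulation needs times about 1.5-fold longer for each of the three dichotomised factors. If the factors matter little, nothing is gained, and a van Elteren test loses a little. This also stands, so the size must be given as a range.

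Third, the fall in unadjusted power with rising R2 partly reflects holding the residual SD fixed. With total SD fixed, unadjusted power rises, and the gap at R2 = 0.3 is about 8 points (84 versus 92%). The shortfall relative to adjustment remains under both conventions.

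Fourth, one model does not represent every endpoint. Forceps number and duration are zero for every patient who meets the primary outcome (34.6% and 62.5% in the pilot). Forceps duration was not simulated, and nothing in the article shows that submucosal thickness depends on the factors. The count and time figures illustrate; they do not predict.

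Fifth, an article condenses the plan, and supplementary adjusted analyses may sit elsewhere. That carries less weight here, because the article names the main tests.

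A reader might infer that every secondary test is at fault, Fisher's included, or that the secondary tests certainly run below 5%. The documents do not support either. One curability outcome has no named test, Fisher's behaviour has another cause, and the rest depends on an unstated R2. Nor can one say that the planned confidence intervals are too wide, since this section specifies none for these outcomes.

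**Conclusion.** The point holds in a limited form. For procedure time, forceps number and duration, dissection speed, submucosal thickness and injection volume, the named tests ignore the allocation factors and are conservative to the extent that those factors are prognostic. The cost is nil at R2 = 0, small at 0.1 or less, and material from about 0.2 to 0.3. Near 0.3 the size is about 2% and the power shortfall is roughly 10 or more points with residual SD fixed. These figures assume 62 evaluable patients per arm, close balance on the factors, and the outcome models shown.

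The treatment estimate is not biased, no false positives arise, and the primary conclusion is untouched. This is a worthwhile gain in efficiency and consistency; it does not make the plan invalid.

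**What to change.** - **Speed, thickness, injection volume:** linear regression with arm plus location, size and antithrombotic use, coded as in the minimisation. Report the adjusted difference with its 95% CI.
- **Procedure time, forceps number and duration:** a van Elteren test or rank ANCOVA on the same factors. Choose one in advance.
- **Binary outcomes:** keep Fisher's exact test.

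The article's Trial status section says that recruitment ended on February 21, 2023. Patients and investigators are unblinded, and most outcomes are recorded at the procedure. The change should therefore be documented with its date before any comparative analysis, and the tests named in the article should be reported alongside.

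The cost is a few lines of text and a second set of results. The factors are already recorded because allocation needed them. If they prove not to be prognostic, van Elteren gives up about 3 to 4 points of power, and regression or rank ANCOVA essentially none.
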